#### Follow-up 1 (T6), 2 (T7) and 4 (T9; duration ca. 10 min)

All participants (groups 1 to 6) will be asked to answer questions regarding (possible) relapse and amount of substance consumed using REDCap electronic data capture tools hosted at the Central Institute of Mental Health [97, 98]. Subsequently, they will complete an interview via telephone four, eight and 24 weeks after T5. Relapse and amount of substances consumed will be recorded. Craving will also be assessed. A full list of assessments is provided in Table 1.

#### Follow-up 3 (duration ca. 60 min; time point T8)

For the third follow-up interview after 12 weeks, all participants will be invited to come to the institute again to complete the above mentioned, computer-based neuropsychological assessment (T8). A second EEG recording will take place during the same neuropsychological task. Further, relapse and amount of substances consumed as well as craving will be assessed again. A full list of assessments is provided in Table 1.

### Statistical analyses

The behavioral and EEG results of the inhibitory control paradigm [78] and craving ratings are defined as primary outcome measures. The results of the inhibitory control paradigm will be compared between testing days before (T1) and after fifth (T5) stimulation or training and after a follow-up period of 12 weeks (T8). Craving rates will be compared before and after the first stimulation/training (T1) and across the subsequent stimulation/training sessions (T2-T5), as well as during the follow-up period (T6-T9). Secondary outcomes include duration of abstinence and amount of substance consumed during the follow-up period.

Regarding the EEG data, resampling (to 250 Hz), filtering (70 Hz high- and 0.1 Hz low-pass filter; 50 Hz notch filter), re-referencing to an average reference, manual inspection, independent component analyses, and segmentation (from –200 to 1200 ms) will be conducted. Removed channels due to technical and regular artifacts (e.g., movement artifacts, excessive noise) will be interpolated using neighboring electrodes. ERP components will be scored as mean amplitudes between 200–300 ms and 300–500 ms over fronto-central and central-parietal electrodes for the N200 and P300 components, respectively. All data (EEG, neuropsychological and psychometric data) will be analyzed using t-tests, repeated measures analysis of variance (rmANOVA) and Pearson correlations. The influence of treatment modality (tDCS add-on intervention over various locations versus inhibition training versus standard treatment) on relapse will be tested with a Cox Regression (outcome variable: time until first relapse). Due to the included individuals and the matched-group design, potential influencing factors on primary and secondary endpoints (e.g., type of substance, severity of SUD, number of comorbidities) will be included in the analyses as covariates. In secondary analyses, we will also take a closer look at the potential influence of these factors on treatment response. In this way, it might be possible to identify subgroups that respond particularly well to the treatment (‘treatment responders’) with the goal of precision-targeted treatments for addiction. Statistical analysis will be conducted using SPSS (IBM Corp., Armonk, N.Y., USA).

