### Hypotheses

#### Primary: effects of tDCS on inhibitory control and substance craving

Anodal tDCS over the right DLPFC as an add-on-therapy improves inhibitory control in SUD in comparison to anodal stimulation over the left DLPFC or occipital cortex, inhibition training, sham stimulation or TAU alone at T5 and T8.Anodal tDCS over the right DLPFC as an add-on-therapy increases fronto-central N200 and central-parietal P300 ERP amplitudes for substances cues and inhibitory control during task-associated EEG measurements at T5 and T8.Anodal tDCS over the right as well as the left DLPFC as an add-on-therapy reduces craving in SUD in comparison to stimulation over the occipital cortex, inhibition training, sham stimulation or TAU alone from T1 to T9.

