## Methods

### Sample size

The sample size estimation in based on the above-listed primary directed hypotheses. According to previous results on craving and inhibitory control [53, 54, 58, 60, 62], the effect size is estimated to be small to medium, f = 0.15. A sample size calculation was performed using the software G*Power http://www.gpower.hhu.de), which yielded 25 participants per group (power 80%, alpha 5%. repeated measures ANOVA and within-between interaction). In order to achieve this sample size, a total of 162 individuals (27 per group) will be assessed, whereby data losses are assumed (e.g., due to a lack of compliance, hardware failure).

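### The later craving windows (T2-T5, T6-T9) are not tied to the T1 baseline, and no model term is fixed for testing hypothesis 3; a T1-adjusted comparison would settle both at no data cost

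*Protocol article*

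**What the plan says.** All of this is in the protocol article.

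- **Statistical analyses** places the behavioural and EEG results of the inhibitory control task "and craving ratings are defined as primary outcome measures".
- **Hypotheses (primary), hypothesis 3** predicts that right and left anodal DLPFC stimulation reduce craving against occipital stimulation, "inhibition training, sham stimulation or TAU alone from T1 to T9". T1 is therefore part of the claim.
- **Statistical analyses, inhibitory control task:** results "will be compared between testing days before (T1) and after fifth (T5) stimulation or training and after a follow-up period of 12 weeks (T8". Here T1 is explicitly joined to T5 and T8.
- **Statistical analyses, craving:** three parts are listed. The first is a pre/post comparison around the opening session at T1. The other two are given only as "across the subsequent stimulation/training sessions (T2-T5), as well as during the follow-up period (T6-T9". The pre-treatment rating appears only in the first of these three parts.
- **Statistical analyses, methods:** all data "will be analyzed using t-tests, repeated measures analysis of variance (rmANOVA) and Pearson correlations". No term of the repeated measures ANOVA is assigned to craving.
- **Sample size** rests on the primary directed hypotheses and names "repeated measures ANOVA and within-between interaction". This is the only model term the article gives.
- **Experimental procedure** states that group 6 (TAU only) has no contact between T2 and T4, although Table 1 marks craving at those visits.

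**The concern.** Two sentences in the same paragraph treat two primary outcomes differently. One anchors the later measurements to T1 and the other does not. Combined with the interaction named in Sample size, the craving sentence can be read as three separate analyses, two of them without a baseline.

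On that reading the test misses the outcome the trial hopes for. A group-by-time interaction within T6-T9 asks whether the arms run in parallel between weeks 4 and 24. If craving falls by T5 and stays down, they do run in parallel and the null is true. A significant result in that window could instead mean that an effect is fading or that controls are catching up. The T2-T5 window similarly shows only divergence after the second session.

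If the sentence is not read that way, a primary outcome is left with several possible tests of very unequal power and no indication of which one answers hypothesis 3.

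**Working it through.** **1. Reproduce the plan's own figure.** Given in Sample size: f = 0.15, alpha 5%, power 80%, six groups, 25 per group (150), within-between interaction. Not given: number of measurements m and correlation ρ. Assume m = 2, ρ = 0.5 and sphericity.

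- λ = f²·N·m/(1−ρ) = 0.0225 × 150 × 2 / 0.5 = 13.5
- df = (6−1)(2−1) = 5 and (150−6)(2−1) = 144
- Power = 80.6%. The smallest N reaching 80% is 149, rounded up to 150, or 25 per group.

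With ρ = 0.5, m = 3 needs 21 per group, m = 4 needs 19 and m = 10 needs 12. The stated 25 fits a two-measurement, pre/post interaction. This is suggestive only, because another ρ with another m comes close (ρ = 0.3 and m = 4 gives 26).

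**2. Set up the craving comparison.** Assumptions: 25 per arm, complete data, SD 1, equal correlation 0.5 between all ratings, and craving lower by a constant d in groups 1 and 2 at every rating after the pre-session T1 rating. Values of d: 0.3, 0.5 and 0.64. The last corresponds to the plan's f: two of six groups shifted by d have group means with SD d·√(2/9) = 0.471d; in a two-measurement interaction this is halved to 0.236d, and 0.15/0.236 ≈ 0.64.

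**3. Noncentrality.** Let B = 150 × (2/9) × d², so B = 8.33 at d = 0.5.

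- *Interaction within T6-T9 or within T2-T5:* the shift is the same at every time point, so the interaction component is zero and λ = 0. Rejection equals alpha.
- *Interaction over T1 and T6-T9 (m = 5):* the time pattern 0,1,1,1,1 has a sum of squares about its mean of 0.8. λ = 8.33 × 0.8/0.5 = 13.3 on 20 df.
- *Interaction over all ten ratings (T1 pre and post, T2 to T9):* sum of squares 0.9. λ = 8.33 × 0.9/0.5 = 15.0 on 45 df.
- *Group main effect over T6-T9:* the variance of a mean of four is 0.5 + 0.5/4 = 0.625. λ = 8.33/0.625 = 13.3 on 5 df.
- *Mean of T6-T9 adjusted for T1:* residual variance is 0.625 − 0.5² = 0.375. λ = 8.33/0.375 = 22.2 on 5 df.

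**4. Rejection rates** (simulation, 3,000 trials per value of d, each test at 5%):

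| Test | d = 0.3 | d = 0.5 | d = 0.64 |
|---|---|---|---|
| Interaction, T2-T5 only | 5.1% | 5.7% | 4.5% |
| Interaction, T6-T9 only | 5.5% | 4.7% | 5.2% |
| Interaction, all ten ratings | 15% | 41% | 69% |
| Interaction, T1 + T6-T9 | 19% | 53% | 81% |
| Group main effect, T6-T9 | 34% | 79% | 97% |
| T1-adjusted mean of T6-T9, six-group omnibus | 56% | 96% | 99.8% |

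The noncentral F values from step 3 at d = 0.5 agree: 41%, 53%, 80% and 96% for the last four rows. With d = 0, all six tests reject between 4.6% and 5.5%.

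**5. Why the single-series option loses.** Its noncentrality is similar to that of the main effect (15.0 against 13.3), but it is spread over 45 degrees of freedom instead of 5. In addition, group 6 has no T2-T4 contact, so a complete-case repeated measures ANOVA over all visits would drop an arm that hypothesis 3 names as a comparator.

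**The case against.** The strongest objection is that separate, baseline-free blocks are an inference. The craving sentence has a single verb and covers T1 to T9, the span of hypothesis 3. It mentions no separate models and does not exclude T1 from anything. The abstract defines the outcome as a change in craving, which presupposes a starting value. The interaction is named only as a sample-size setting, and the two-measurement reproduction above suits a pre/post test better than a T6-T9 one. All of this stands.

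A reader might therefore go too far and infer that the plan cannot detect a sustained reduction, or that a real benefit would be reported as no effect. The article does not support either. It lists t-tests and repeated measures ANOVA. In a randomised trial the group main effect from the same T6-T9 model is valid without a baseline and has about 79% power at 0.5 SD. The 5% also follows by construction from a constant shift; an effect that grew or faded across T6-T9 would give some interaction.

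It can also be said that the model term is a detail for the analysis plan. That would be so if the article were simply silent. It is not: it fixes comparison windows for a primary outcome, and as worded they do not match the T1-to-T9 claim that they are meant to test. Finally, preferring a T1 covariate to an ANOVA that includes T1 is partly a matter of choice. Under the stated assumptions, though, it has the highest power of all the options compared.

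**Conclusion.** The point holds as a mismatch of wording that has consequences for power. The craving sentence does not link T2-T5 and T6-T9 to T1, hypothesis 3 does, and the only named model term is one whose power against a sustained reduction ranges from 5% to 53% at 0.5 SD, depending on how the sentence is read. The unadjusted main effect gives about 79%, and the T1-adjusted mean about 96%. What the baseline adds over the main effect is precision; it is not what makes detection possible. The claim that the planned analysis is blind to a lasting effect is true only for the within-window interaction under a constant effect, and the article does not commit to that test.

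The figures rest on an assumed correlation of 0.5, assumed effects of 0.3 to 0.64 SD, complete data in 25 per arm, and equal effects in groups 1 and 2. Under a constant effect, the zero power of the within-window interaction does not depend on the correlation or the effect size. The other percentages do.

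**What to change.** In Statistical analyses, state that hypothesis 3 is tested by comparing craving at T5 and mean craving over T6-T9 between groups, with pre-session T1 craving as covariate and with the contrasts that hypothesis 3 names (right and left DLPFC stimulation against occipital stimulation, inhibition training, sham and TAU). For group 6, which has no session, the scheduled T1 rating serves as the covariate. Keep the T1 pre/post comparison and the courses within T2-T5 and T6-T9 as supporting analyses.

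The cost is analysis wording only. Table 1 already schedules craving at T1, T5 and T6-T9, and these time points avoid the T2-T4 gap in group 6, so all six arms stay in the test. The small downside is that the within-window time courses are no longer the primary craving test, so a change in the effect during follow-up would be described in the supporting analyses.

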	Edinburgh Handedness Inventory (EHI, [79])	X					
Questionnaires Alcohol/Substance	Craving Scale [80] Alcohol Urge Questionnaire (AUQ, [81])	X X	X X	X X	X X	X X	X X
	Fagerstrøm Test of Cigarette Dependence (FTND, [82])	X				X	
	Craving Automated Scale for Alcohol (CAS-A, [83])	X				X	X
	Obsessive Compulsive Drinking Scale (OCDS, [84])	X					
	Alcohol Dependence Scale (ADS, [85])	X					
Questionnaires Clinic	Beck Depression Inventory–II (BDI-II [86]) Quality of life [87]	X X		X		X X	
	Perceived Stress Scale (PSS, [88])	X				X	
	Barratt Impulsiveness Scale (BIS, [89])	X		X		X	
	Creature of Habit Scale (COHS, [90])	X				X	
	ASRS-V1.1 Screener (WHO, 2004) Childhood Trauma Questionnaire (CTQ, [91])	X X					
Outcome consumption	Form 90 interview [92]	X		X	X	X	X
	Time to relapse	X		X	X	X	X
	Percentage of abstinence/heavy drinking days	X		X	X	X	X
Neuropsychological assessment	Delay Reward Discounting Task [93]	X		X		X	
	Dimensional Card Sorting Task [94]	X		X		X	
	Dot-probe task [95]	X		X		X	
	Stop-signal task [96]	X		X		X	
Electroencephalography (EEG)	Modified Go/NoGo paradigm [78]	X		X		X	
Interventions	TAU + active tDCS (Groups 1–3)	X	X	X			
	TAU + sham tDCS (Group 4)	X	X	X			
	TAU + computerized inhibition training (Group 5) TAU (Group 6)	X X	X X	X X			
	Adverse events	X	X	X			

*T1* = *first investigation day, T2-4* = *second to fourth investigation days, T5* = *fifth investigation day, T6-7* = *follow up after 4 weeks (T6) and 8 weeks (T7) *via* phone, T8* = *follow up after 12 weeks on site, T9* = *follow up after 24 weeks *via* phone*

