#### Day 5 (T5; duration ca. 1 h)

Participants will receive the fifth and last 20-min long tDCS (groups 1 to 3), sham tDCS (group 4), or an inhibition training (group 5) (e.g., Friday). Following, the same computer-based neuropsychological assessment will be completed (T3), and craving will be re-assessed. A full list of assessments is provided in Table 1. Adverse events that occurred since T4 are documented at the beginning of the investigation day. As participants are not contacted again until 28 days after T5 for the first follow-up assessment, any adverse events related to the final session are assessed and documented at the end of the T5 assessment.

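### The EEG filter cut-offs for a primary outcome are mislabelled, and the visit text contradicts the hypothesis, Table 1 and the analysis section on whether EEG is recorded at T5

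*Protocol article*

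**What the plan says.** **Filter.** In the protocol article, Statistical analyses, the EEG preprocessing includes "resampling (to 250 Hz") followed by a "70 Hz high- and 0.1 Hz low-pass filter; 50 Hz notch filter". The outcome is then defined from the filtered signal: "ERP components will be scored as mean amplitudes between 200–300 ms and 300–500 ms", for the N200 and P300 respectively. The same section makes the EEG results of the inhibitory control paradigm a primary outcome, alongside its behavioural results and craving.

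**EEG schedule, places that give three recordings.** Hypothesis 2 states that right anodal stimulation "increases fronto-central N200 and central-parietal P300 ERP amplitudes for substances cues and inhibitory control during task-associated EEG measurements at T5 and T8". In Table 1 the electroencephalography row ("Modified Go/NoGo paradigm [78"]) is marked at T1, T5 and T8. The Statistical analyses section compares the paradigm at T1, T5 and T8.

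**EEG schedule, places that give two.** The description of the first day places an EEG recording at T1. The Day 5 section says that after the last session "the same computer-based neuropsychological assessment will be completed (T3"), and does not mention EEG. The Follow-up 3 section says of T8: "A second EEG recording will take place during the same neuropsychological task".

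**The concern.** Both problems concern how a primary outcome is obtained.

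The filter statement is a processing rule in the public record against which the analysis will be judged. Applied literally, it removes the signal that the next sentence of the plan sets out to score.

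The schedule matters more in practice. T5 is the only EEG between the end of the intervention and the 12-week visit, and the article itself names dropout as a main risk to the study. Two sites with different EEG systems need one unambiguous schedule. A recording omitted at T5 because a site followed the visit text could not be made up later. The T3 label adds to the confusion, because Table 1 uses T3 for one of the treatment days on which no EEG or task battery is planned.

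**Working it through.** **1. Filter as written.**

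Inputs from Statistical analyses: high-pass 70 Hz, low-pass 0.1 Hz, notch 50 Hz, sampling rate 250 Hz after resampling, scoring windows 200–300 ms (N200) and 300–500 ms (P300).

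- Pass bands: at or above 70 Hz, and at or below 0.1 Hz. Their intersection is empty.
- Where the components lie: taking each scoring window as about half a cycle, a 100 ms window corresponds to 1/(2 × 0.1 s) = 5 Hz and a 200 ms window to 1/(2 × 0.2 s) = 2.5 Hz. Both fall between 0.1 and 70 Hz, in the range that the literal rule rejects.
- Notch: 50 Hz also lies between 0.1 and 70 Hz. A 50 Hz notch has a purpose only if that range is kept.

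**2. Numerical check.**

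The article gives neither filter order nor waveform, so these are assumptions: second-order Butterworth filters run forward and backward at 250 Hz, on a synthetic waveform in arbitrary units. The waveform has a negative peak of 4 at 250 ms (SD 30 ms) and a positive peak of 8 at 400 ms (SD 60 ms).

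| Setting | Mean, 200–300 ms | Mean, 300–500 ms |
|---|---|---|
| Unfiltered | −2.11 | 5.38 |
| As written (70 Hz high-pass, 0.1 Hz low-pass) | about −3 × 10⁻¹² | about 6 × 10⁻¹² |
| Labels exchanged (0.1 Hz high-pass, 70 Hz low-pass) | −2.31 | 5.18 |

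The exact residuals depend on the assumptions. The conclusion does not, because the literal pass bands are disjoint whatever the waveform.

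**3. EEG schedule, set side by side.**

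| Place | T1 | T5 | T8 | Recordings |
|---|---|---|---|---|
| Hypothesis 2 | not named | yes | yes | at least 2 |
| Table 1, EEG row | yes | yes | yes | 3 |
| Statistical analyses | yes | yes | yes | 3 |
| Visit text (first day, Day 5, Follow-up 3) | yes | not named | yes, called the second | 2 |

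If EEG is recorded at T1 and T5, the T8 recording is the third. Calling it the second therefore contradicts Table 1 outright and is more than an omission.

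**4. Can the sample size settle the count?** No. With six groups, f = 0.15, 80% power and alpha 5%, the stated 25 per group is reproduced with two measurements and a correlation of 0.5 (power 0.806). The article states neither the number of measurements nor the correlation. With three measurements the requirement runs from 41 per group (correlation 0) to 13 (correlation 0.7).

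**5. Time at T5.** The Day 5 section plans about one hour, including a 20-minute session in groups 1 to 5. That leaves about 60 − 20 = 40 minutes for everything else in those groups. No duration is given for the task battery or for the EEG, so no shortfall can be computed.

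**The case against.** The strongest reply is that the document already contains the intended plan.

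On the schedule, the Day 5 section repeats the same assessment as at T1, part of which is recorded with EEG by the article's own description. It then sends the reader to Table 1 for the full list, and Table 1 marks EEG at T5. Only one ordinal word in Follow-up 3 points the other way.

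On the filter, the 50 Hz notch and the scoring windows leave only one coherent reading. Filtering is offline, and a literal run would return essentially zero, which would be noticed at once and could not quietly bias a result.

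This reply stands against three stronger inferences a reader might draw:

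- **That hypothesis 2 cannot be tested.** The article does schedule and analyse EEG at T5 and T8, and the filter labels can be exchanged on stored data.
- **That T5 EEG is lost for all 162 participants.** This would require both sites to disregard Table 1, the hypothesis and the analysis section. Nothing in the document shows that.
- **That T5 needs at least 20 + 60 = 80 minutes.** This carries the whole T8 visit over to T5. Table 1 gives T8 five questionnaires that T5 lacks (Fagerstrøm test, CAS-A, quality of life, Perceived Stress Scale, Creature of Habit Scale), and both durations are approximate. The Go/No-Go task is run at T5 in any case, and some electrode set-up may be shared with the stimulation cap.

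The reply does not remove the errors themselves. The filter rule is wrong as stated, and the word for the T8 recording cannot be true together with Table 1.

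**Conclusion.** The point holds as two specific errors in the text that defines a primary outcome.

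First, the filter labels are reversed. The literal rule leaves no N200 or P300 signal and the exchanged labels keep both. This is very probably a wording slip, and it is fully recoverable.

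Second, the visit text supports two EEG recordings, while Table 1 and the analysis section require three and hypothesis 2 names T5 explicitly. The weight of the document favours EEG at T5, so this is an inconsistency to reconcile. Data would be lost only if a site followed the visit text without Table 1, but that loss would be permanent, and for this reason the correction should not wait for the analysis stage.

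The T5 slot looks tight and deserves a check, but the document supports no figure for a shortfall. The filter conclusion rests only on the stated cut-offs. The schedule conclusion rests on reading the passages against each other.

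**What to change.** - **Statistical analyses:** write *0.1 Hz high-pass and 70 Hz low-pass filter; 50 Hz notch filter*.
- **Day 5 (T5):** change the label T3 to T5, and state that EEG is recorded during the modified Go/No-Go task.
- **Follow-up 3 (T8):** call this the third EEG recording.
- **Sites:** confirm that Mannheim and Wiesloch both record EEG at T5, before the T5 visits or as early as possible if these have begun.
- **T5 duration:** check the planned hour against the actual time for the session, EEG set-up and task battery, and amend it if needed.

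The cost is four wording corrections, one confirmation from the sites and one check of visit time. The design, sample size and analysis time points do not change.

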**Fig. 1 Fig1:**
[figure not shown]
Study design including four follow-ups over a period of 6 months

On the *first day* (T1/baseline assessment; e.g. Monday), all individuals are comprehensively informed about the goals of the proposed study and all study-related measures. Individuals will give their written informed consent and will receive a copy of the relevant study information and consent agreement. Subsequently, diagnostic interviews will be performed to assess eligibility for study participation, pre-existing conditions (mental, neurological and somatic in nature), validate the diagnoses of SUD, and assess current consumption habits. Pregnancy and drug tests will also be completed. Eligible participants will be asked to complete questionnaires and computer-based neuropsychological assessments (see Table 1). Participants will receive an EEG recording during one part of the neuropsychological assessment, namely during a modified Go/No-Go paradigm including various working memory loads [78] to assess the interaction between working memory load and response inhibition programmed in Presentation® software (Neurobehavioral Systems, Inc., Berkeley, CA, USA). At the Wiesloch study site, EEG recordings are conducted using a mobile EEG system (24 channels with active electrodes; sampling rate 1000 Hz; mBrainTrain, Belgrade, Serbia). At the Mannheim site, stationary EEG assessments are performed using BrainVision Recorder software package (32 channels with active electrodes; sampling rate 1000 Hz; Brain Products GmbH, Gilching, Germany). Two channels are occupied by the tDCS electrodes for both systems (for groups 1,2 and 4: F3 and F4; for group 3: Cz and O1). After completing all assessments, participants receive their first add-on treatment. For the first tDCS session, the tDCS study groups (groups 1 to 3) will receive a 20-min long tDCS with 0.08 mA/cm2, over the respective brain areas. The inhibition training group will perform a go-/no-go training according to Stein et al. [13] and the sham group will receive a 20 min long sham tDCS. Before and after the stimulation or training, craving will be assessed (see Table 1).

**Table 1 Tab1:** Measurements and interventions

		T1	T2-T4	T5	T6-7	T8	T9
Baseline information and medical screening	Sociodemographic data	X					
	Internistic, neurological examination	X					
	Drug/pregnancy urine screening	X		X		X	
	Menstrual cycle	X					
	Structured Clinical Interview for DSM-5	X					

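### Every primary outcome has a pre-treatment T1 value, but the planned rmANOVA uses it as a level of time, not as a covariate; the test is valid but gives up precision, by an amount that depends on an unstated correlation

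*Protocol article*

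**What the plan says.** The protocol article, Statistical analyses, defines the behavioural and EEG results of the inhibitory control task and the craving ratings as primary. On method it says "All data (EEG, neuropsychological and psychometric data) will be analyzed using t-tests, repeated measures analysis of variance (rmANOVA) and Pearson correlations". For the task, "The results of the inhibitory control paradigm will be compared between testing days before (T1) and after fifth (T5) stimulation or training", and again at T8. Craving is compared before and after the first session at T1, across T2 to T5, and over follow-up T6 to T9.

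The sentence on adjustment reads "potential influencing factors on primary and secondary endpoints (e.g., type of substance, severity of SUD, number of comorbidities) will be included in the analyses as", and the word that completes it makes these factors covariates. The list is introduced as examples, and the T1 value of the outcome is not one of them.

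Sample size confirms the structure of the model: the calculation gave "25 participants per group (power 80%, alpha 5%. repeated measures ANOVA and within-between interaction", for an assumed f of 0.15. An interaction of group with time needs T1 among the time levels.

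Experimental procedure and Table 1 place the questionnaires, the neuropsychological tasks and the EEG at T1, ahead of the first add-on treatment. For craving on that day, "Before and after the stimulation or training, craving will be assessed". A pre-treatment value is therefore planned for every primary outcome.

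**The concern.** A baseline taken before treatment can be used in two ways. As a level of the time factor, it is one more response, and the treatment effect is read from the group-by-time interaction. As a covariate, it explains variation in the later values. With T1 and one later visit, the interaction test is the comparison of change scores between groups. This subtracts the whole T1 value, noise included, whereas the covariate model subtracts only the part that predicts the later value.

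At stake is the precision of the tests of primary hypotheses 1 to 3, in arms of 25 to 27 with an allowance of two participants per arm for data loss. No stratification on T1 craving or inhibition is described, so chance differences between six small arms can occur. Given such a difference, a change score over-corrects: an arm that happens to start high on craving tends to show a larger fall.

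**Working it through.** **Inputs from the article:** six equal groups; "the effect size is estimated to be small to medium, f = 0.15"; alpha 5%; 25 per group (N = 150) analysed and 27 per group (N = 162) enrolled.

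**Inputs not in the article, so assumed:** the number of measurements m and the correlation rho between them, with equal variance at each visit.

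**Step 1, reproduce the plan's figure.** For the within-between interaction, lambda = f² × N × m / (1 − rho), with (k−1)(m−1) and (N−k)(m−1) degrees of freedom. With m = 2 and rho = 0.5:

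- lambda = 0.0225 × 150 × 2 / 0.5 = 13.5, with 5 and 144 df; power 0.806.
- At 24 per group (N = 144), power is 0.786. The smallest N for 80% is 149, which is 25 per group as stated.

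**Step 2, variance ratio for T1 against one later visit.**

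- Change score: 2(1 − rho)σ².
- T1 as covariate: (1 − rho²)σ².
- Ratio: (1 − rho²) / [2(1 − rho)] = (1 + rho)/2, below 1 for every rho below 1. At rho = 0.5 it is 0.75.

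**Step 3, power with T1 as covariate.** For the same raw effect, lambda is multiplied by 2/(1 + rho), and one error df is spent.

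- N = 150: 13.5 × 2/1.5 = 18.0, with 5 and 143 df; power 0.916 against 0.806 (+11.0 points).
- N = 162: 14.58 × 2/1.5 = 19.44; power 0.938 against 0.841 (+9.7 points).
- The smallest N for 80% falls from 149 to 113, about 19 per group.

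A simulation of 4,000 trials at N = 150 and rho = 0.5 gave 0.799 for the change-score test and 0.911 for the adjusted test.

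**Step 4, range over rho (m = 2, f fixed at 0.15, N = 150).**

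| rho | T1 as time level | T1 as covariate | Gain (points) |
|---|---|---|---|
| 0.3 | 0.639 | 0.847 | 21 |
| 0.4 | 0.718 | 0.878 | 16 |
| 0.5 | 0.806 | 0.916 | 11 |
| 0.6 | 0.895 | 0.955 | 6 |
| 0.7 | 0.967 | 0.986 | 2 |

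With f fixed, a high rho leaves little room because the planned test is already near 100%. If the planned test is instead held at 0.806 whatever rho is, the adjusted test has 0.952, 0.916, 0.874 and 0.828 at rho 0.3, 0.5, 0.7 and 0.9, gains of about 15, 11, 7 and 2 points.

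**Step 5, three measurements (T1, T5, T8).** Here rho of about 0.4 also reproduces 25 per group (0.803). For an effect equal at T5 and T8, adjustment raises power from 0.803 to 0.971 on 10 numerator df, or from 0.895 to 0.991 if both analyses use the mean of T5 and T8 on 5 df.

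**Step 6, a single contrast of the kind hypothesis 1 makes.** Suppose Group 1 alone differs from five equal groups. At rho = 0.5 and m = 2, f = 0.15 then implies a difference of sqrt[(13.5/25)/(5/6)] = 0.805 SD. By the normal approximation at two-sided 5%, pairwise power rises from 0.812 to 0.908 at 25 per arm and from 0.841 to 0.927 at 27.

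**The case against.** The strongest reply is that nothing here is an error. The interaction test is valid and unbiased under randomisation, the trial was sized for that test, and the stated 25 per group reproduces at 80% power. The plan meets its own target, and what it gives up is power above that target. This stands, and it makes the point one of efficiency. A reader might infer that the planned analysis is biased, or that the trial is underpowered for its stated test. The documents support neither. The over-correction for a chance T1 difference is conditional on that difference arising and averages out over randomisations.

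A reader might also take a loss of about 10 points as a property of this trial. It is not: m = 2 and rho = 0.5 were chosen because they return the stated sample size, other pairs return it too, and the gain could be near 2 points or above 20. The exact change-score identity covers T1 and one later visit, while the plan has T5 and T8 for the task and more ratings for craving. The omnibus figure is also only a proxy for the directed contrasts in the hypotheses, and the contrast in step 6 needs an assumed pattern of means.

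Finally, the covariate list is open, and an analysis plan that is not shown may add to it. That stands in part. But the article itself commits to rmANOVA across T1 and later visits and bases its sample size on it, and adding covariates to a model that keeps T1 among the responses does not turn it into a baseline-adjusted analysis.

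**Conclusion.** The point holds as a near-costless gain in precision. The article has a pre-treatment value for every primary outcome and commits to a model that uses it less efficiently than it could. The direction is certain for T1 against one later visit, at any rho below 1 with equal variances. The size is not known from the documents. It is 11 points at 25 per group and 10 at 27 per group under two measurements and rho = 0.5, with a range at 25 per group and fixed f of about 21 points (rho 0.3) to about 2 (rho 0.7). The planned test remains valid.

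**What to change.** In Statistical analyses, replace the primary model. For each primary outcome, take the post-baseline values as the response: T5 and T8 for the task and EEG, and the ratings after the T1 baseline for craving. Fit group, visit and group-by-visit, with the participant's own pre-treatment T1 value of that outcome as covariate. Report baseline-adjusted group differences at the visits each hypothesis names. The covariates already planned can stay.

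Craving needs two further rules:

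- **Baseline.** Use the T1 rating taken before the session, and treat the T1 rating after it as post-baseline. Group 6 has no session, so its single T1 rating is its baseline.
- **Group 6 at T2 to T4.** Experimental procedure gives this arm no contact at those visits, so a complete-case repeated-measures model over all later ratings would drop it. Either fit a mixed model that does not need complete cases, or restrict contrasts with Group 6 to T5 to T9. Under either option, no contrast with Group 6 is available at T2 to T4.

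The cost is a rewritten model statement and one degree of freedom per outcome, or a few more if the baseline slope may differ by visit. Results are then read as adjusted differences at a visit, not as change from T1. No visit, measurement or participant is added, and SPSS, the software already named, can fit the model.
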